### Confirmation of implementation

The provider, manager, and principal investigator will confirm that the trial is appropriately implemented. They will also confirm that regenerative medicine is provided in accordance with the regenerative medicine provision plan.

### Sample size estimation

The target sample size for this study is 15. Since patients will individually undergo LLIF at 1 to 4 intervertebral levels, more than 40 intervertebral levels are expected to be included in this study. Therefore, at least 80 bone graft spaces will be included to evaluate bony fusion.

A sample size calculation was performed based on the results of previous studies [2, 12]. In previous studies, the fusion rate of LLIF with Affinos® was 70.9%. And, the intervertebral fusion rate with autologous iliac crest bone was 94.5%. Based on these parameters, we calculated a sample size of 40 bone graft spaces per group with a power of 80% and an alpha of 5% (two-tailed).

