### Study procedures

The outline of this study is shown in Fig. 1. Consecutive patients scheduled for LLIF in the University of Tsukuba hospital will be enrolled in this trial. The target sample size for this study trial is fifteen patients, with a total of 40 intervertebral levels. This trial is approved by the institutional review board of the University of Tsukuba Hospital, and consent for participation in the trial will be obtained from all patients (jRCTb032200199).

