### Missing data and data from participants who discontinue

All patients will be followed up as per the normal postoperative course, ensuring necessary data acquisition for the research. Additionally, to avoid missing data and to promote participant retention, data managers will announce the required tests, questionnaires, and their schedules to attending doctors and patients. Missing data will not be supplemented, and rejected data will be excluded.

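### The 80% power is calculated for 40 independent spaces per group, but the design gives matched pairs nested in 15 patients, and the minimum of 80 spaces does not follow from the level count

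*Protocol article*

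**What the plan says.** Under Sample size estimation, the protocol article takes two rates from previous studies: "the fusion rate of LLIF with Affinos® was 70.9" per cent, and "the intervertebral fusion rate with autologous iliac crest bone was 94.5" per cent. From these, "we calculated a sample size of 40 bone graft spaces per group with a power of 80% and an alpha of 5% (two-tailed").

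The same section sets 15 patients as the target and notes that each has 1 to 4 levels operated on. It expects this to yield more than 40 levels, and concludes: "Therefore, at least 80 bone graft spaces will be included to evaluate bony fusion". Study procedures puts it as: "The target sample size for this study trial is fifteen patients, with a total of 40 intervertebral levels".

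Four other statements bear on the calculation:
- Study procedures: the two graft spaces of each cage receive one block with PRP and one without.
- Study procedures: a space counts as fused only if flexion–extension films show no instability, which is a property of the whole level.
- Statistical analyses: the primary comparison is a chi-square test of fusion rates between the two kinds of graft.
- Missing data: "Missing data will not be supplemented, and rejected data will be excluded".

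**The concern.** The calculation treats the spaces as two independent groups of 40. In this trial the two groups are the two halves of the same cages, those cages sit in 15 patients, and both halves of a cage share the instability criterion. The 80% therefore belongs to a different design.

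Two inputs also carry more weight than the text shows. An expected number of levels becomes a guaranteed number of spaces, although nothing in eligibility guarantees it and unobserved spaces drop out of the analysis. The rate entered for the PRP graft was measured on autologous iliac crest bone; the article gives no PRP rate.

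The Discussion calls the trial confirmative. If the result is not significant, a reader will weigh it against the stated 80%. If that figure does not apply, a null result could be taken as stronger evidence against PRP than it is.

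**Working it through.** **Inputs from the protocol article.** Control 0.709; target 0.945; two-sided alpha 0.05; power 0.80; 40 spaces per group; 15 patients; 1 to 4 levels each; two spaces per level. The article gives no pair correlation, PRP fusion rate, distribution of levels per patient or allowance for loss. Values used for these below are assumptions.

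**1. The plan's own figure.** Two independent proportions, pooled variance under the null, no continuity correction:

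n = [1.960·√(2p̄(1−p̄)) + 0.842·√(p₁(1−p₁)+p₂(1−p₂))]² / (p₂−p₁)²

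- p̄ = (0.709+0.945)/2 = 0.827, so 2p̄(1−p̄) = 0.2861
- p₁(1−p₁)+p₂(1−p₂) = 0.2063+0.0520 = 0.2583
- p₂−p₁ = 0.236, squared 0.0557
- n = (1.048+0.428)²/0.0557 = 2.179/0.0557 = 39.1, so 40

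The stated 40 reproduces. With continuity correction it would be 47.2, so 48. The exact power of an uncorrected chi-square with 40 independent spaces per group is 85%.

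**2. Pairing.** With pair correlation φ, the probability that both spaces fuse is p₁₁ = p₁p₂ + φ·√(p₁(1−p₁)p₂(1−p₂)). The discordant probabilities are p₂−p₁₁ (PRP only) and p₁−p₁₁ (control only). Exact McNemar power sums over the binomial number of discordant pairs.

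| φ (assumed) | PRP only | Control only | Power, 40 pairs |
|---|---|---|---|
| 0 | 0.275 | 0.039 | 74% |
| 0.1 | 0.265 | 0.029 | 78% |
| 0.2 | 0.254 | 0.018 | 83% |
| 0.3 | 0.244 | 0.008 | 89% |

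The mid-p version has 81% at φ = 0.

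**3. Patients.** Simulation with 15 patients (ten with 3 levels, five with 2, so 40 pairs) and a cluster-robust t-test on 14 degrees of freedom; correlations are assumed and on a latent normal scale.
- Patient effect shared by both grafts, 0, 0.2 and 0.4: power about 79%, 81% and 83%. A shared effect largely cancels within pairs.
- Patient effect specific to each graft type, 0.2 and 0.4: power about 73% and 66%.

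**4. Number of levels.** 15×1 = 15 and 15×4 = 60, so eligibility guarantees 30 spaces, not 80. Forty levels need 40/15 = 2.67 evaluable levels per patient. Exact chi-square power at 70.9% v 94.5%:

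| Levels | Power |
|---|---|
| 15 | 40% |
| 30 | 73% |
| 35 | 79% |
| 40 | 85% |

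Exact McNemar at 30 pairs has 56% to 70% for φ from 0 to 0.3.

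**5. Target rate.** Exact chi-square power with 40 spaces per group is 60% if PRP reaches 90%, and 33% if it reaches 85%.

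**The case against.** A reader might infer that the trial lacks the power it states. The documents do not support that. At 40 pairs the exact McNemar range of 74% to 89% straddles 80%. Because both spaces share the instability criterion, some positive pair correlation is plausible, and that raises the power of a paired test. The clustered simulation falls clearly below 80% only when the PRP effect is assumed to vary between patients, on which the article is silent.

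A reader might also call the 94.5% a mistake. It is not: its source is stated openly, and the Discussion presents PRP with this artificial bone as a possible alternative to autograft, so powering for an autograft-level rate fits that aim. The Background says no reports show efficacy of PRP with this class of graft in LLIF, so a directly applicable rate may not have existed. Power falls for smaller effects in any trial.

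A low probability of reaching 40 levels cannot be quoted as a finding either. It would need a distribution of levels per patient that the article does not give, and the centre may know its own case mix. A modest shortfall also costs little: 35 levels still give 79% by chi-square.

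Finally, a condensed article may leave a recruitment rule and a loss allowance to the full protocol. Their absence alone is therefore no fault.

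What stands is what the article itself states: a power figure from a formula that does not match the design, and a minimum that is only an expectation.

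**Conclusion.** The arithmetic is right, but it answers a question about independent groups. For matched pairs nested in 15 patients the 80% is not derived, and actual power may lie on either side of it: 74% to 89% by exact McNemar at 40 pairs for assumed correlations of 0 to 0.3, and lower if the PRP effect differs between patients. The minimum of 80 spaces is wrong as written, since eligibility guarantees 30 and missing data are excluded. The target effect amounts to PRP with artificial bone equalling autograft, and power is sensitive to it.

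The pair correlations, patient-level correlations, level counts below 40 and alternative PRP rates are assumptions for illustration. The point should be fixed before results are read against the stated power. It is a mismatch in the basis of the power statement; it does not demonstrate a loss of power.

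**What to change.** Four changes to the sample size text:

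1. Replace the minimum of 80 spaces with an expected number, and give the basis for that expectation.
2. State whether 15 patients or 40 levels with evaluable 1-year imaging is the binding target, and word Study procedures to match.
3. Say that the 40 per group assumed independent spaces, and restate power for a paired, patient-clustered analysis as a range over evaluable levels (for example 30, 35 and 40) and assumed pair correlation.
4. Label 94.5% as an autograft-level target rather than an expected PRP rate, and show power for smaller effects such as 90% and 85%.

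This costs text only; no added enrolment is needed. The price is that a single 80% becomes a range that may look less favourable.

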### Statistical analyses

For baseline characteristics, summary statistics will comprise frequencies and proportions for categorical variables, whilst means and standard deviations will be used for continuous variables. Patient characteristics will be compared using a *χ*^2^ test for categorical variables and a *t*-test or Mann–Whitney *U* test for continuous variables.

The intervertebral fusion rate in each cage space will be calculated using primary endpoint analysis. A *χ*^2^ test will be performed to compare the fusion rates between bone grafts with and without PRP.

For secondary endpoint analysis, a *χ*^2^ test will be performed to compare the fusion rates between bone grafts with and without PRP at 6 months. Multivariate analyses will be performed to assess the relationship of bony fusion with VAS, JOA-BPEQ, ODI, and EQ-5D scores.

Statistical analyses will be performed using SPSS Statistics version 27.0 (International Business Machines Corporation, NY, USA). All *p* values will be two-sided, and *p* < 0.05 will be considered significant.

### Ethics

This trial was approved by the regional ethical review board. The trial will be conducted in accordance with the principles of the World Medical Association (WMA) Declaration of Helsinki.

### Patient informed consent

All patients will be given written explanatory materials and consent forms. The principal investigator will provide patients with sufficient information before obtaining informed consent.

This study will be covered by clinical research insurance. Compensation will be provided to the participants who present with adverse events related to the administration of regenerative medicine in this trial.

### Public disclosure and publication policy

The outline of the trial will be registered on the public registration site, Japan Registry of Clinical Trials (jRCT), prior to the implementation of the trial. jRCT is approved as a member of the Primary Registry Network of WHO ICTRP. The results of the trial will be published in an English journal after the final registration is completed on the jRCT site.

### Protocol amendments

In the case that important protocol modifications are required, approval of the accrediting regenerative medicine committee will be required. The protocol modification, once approved, will immediately be registered on the public registration site, jRCT.

## Discussion

This study is a confirmative trial to elucidate the efficacy of PRP with Affinos® for bony fusion in LLIF. If this study demonstrates the efficacy of PRP, Affinos® impregnated with PRP could be used as an alternative for autologous bone grafts with no risk of complications as opposed to that observed with autologous bone harvest. The current study is important to develop a viable procedure for substantial and safe bony fusion in LLIF.

## Trial status

This trial is currently being conducted. Recruitment of study patients commenced on February 24, 2021. Trial completion will be expected at 1 year after surgery.

## Protocol version

Version. 4.0 (April 15, 2022).

## Data Availability

Only the principal investigator and designated investigators will have access to the final dataset.

## Abbreviations

PRP: Platelet-rich plasma
LLIF: Lateral lumbar interbody fusion
CT: Computerized tomography
PDGF: Platelet-derived growth factor
TGF-β: Transforming growth factor-β
IGF: Insulin-like growth factor
VAS: Visual analog scale
JOA-BPEQ: Japanese Orthopedic Association Back Pain Evaluation Questionnaire
ODI: Oswestry disability index
EQ-5D: European quality of life 5 dimensions
jRCT: Japan Registry of Clinical Trials
